#### Duration of pyrexia (inpatients only)

This will be summarised as time from developing pyrexia (taken as the date of admission to hospital if present at randomisation) using a Cumulative Incidence Function plot and analysed using Fine and Gray regression incorporating terms for study arm and the minimisation factors used for randomisation. (Gray, 1988, a class of k-sample tests for comparing the cumulative incidence of a competing risk. Annals of Statistics 1988; 16:1141-1154)(Fine, 1999, A proportional hazards model for the subdistribution of a competing risk. Journal of the American Statistical Association 1999; 94: 496-509). Patients who die during the course of the 60 day study period, prior to resolution of pyrexia, will be considered as having had a competing risk at the date of death. Participants who never develop pyrexia will not be included in this analysis.

#### WHO COVID 10-point ordinal severity scale at day 8, 29, 60

This will be analysed using the same technique as the primary end-point.

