|----------------------------------------------------------------------------------------------------------------------------|-------------------------------------------------------------------------------------------------------------------------------------------------------------------------------------------------------------|------------------------------------------------|
|                                                                                                                            | Overall survival                                                                                                                                                                                            | Up to and including day 60                     |
|                                                                                                                            | Inpatients only:
Viral clearance on or before d8 **                                                                                                                                               | Day 8                                          |
|                                                                                                                            | Inpatients only:
Duration of pyrexia in days (defined as a temperature $\geq 38^{\circ}\text{C}$ )                                                                                                | Up to and including day 60                     |
| Evaluate the safety and tolerability of favipiravir in the study population                                                | Adverse events                                                                                                                                                                                              | Up to and including day 60                     |
| Exploratory objectives                                                                                              | Exploratory endpoints                                                                                                                                                                                | Timepoint of assessment                 |

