### **3.2 Eligibility criteria**

#### **Inclusion criteria**

1. Age 16 or over at time of consent
2. Exhibiting symptoms associated with COVID-19
3. Positive for SARS-CoV-2 on valid COVID-19 test
4. Point 2, 3, or 4 on the WHO COVID-19 ordinal severity scale at time of randomisation. (Symptomatic Independent, Symptomatic assistance needed, Hospitalized, with no oxygen therapy)
5. Have  $\geq 10\%$  risk of death should they be admitted to hospital as defined by the ISARIC4C risk index: <https://isaric4c.net/risk>
6. Able to provide written informed consent
7. Negative pregnancy test (women of childbearing potential\*)
8. Able to swallow oral medication

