**During these times, only randomisations sent by email will be processed.**

**Please check local site Pharmacy opening times – patients should be randomised no later than 1 hour before local site Pharmacy closes.**

**Out of hours randomisation availability is dependent on site Pharmacy and Nursing staff availability – this may differ between sites and at different times according to the progress of the pandemic. Sites will be kept informed of any changes to this service.**

When the patient has consented, a screening number should first be obtained by contacting the CRUK CTU, Glasgow.

When screening is complete and eligibility confirmed, the CRUK CTU Glasgow should be contacted again. The patient's eligibility criteria will be checked and, if eligible, a trial number and trial arm will be allocated at this point.

All patients must be registered/randomised onto the trial prior to commencement of trial treatment.

A minimisation algorithm incorporating a random component will be used to allocate patients to either experimental or control arm. The factors used in the minimisation will be:

- Site
- Age (16 - 50; 51 – 70; 71+)
- History of hypertension or currently obese (BMI>30 or obesity clinically evident) (yes; no)
- <7 days duration of symptoms (yes; no; unknown)
- Sex (male; female).
- WHO COVID ordinal severity score at baseline (2 or 3; 4)

With the patient's consent, their GP will be informed of their involvement in the trial.

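### Duration of pyrexia: inclusion of inpatients afebrile at randomisation depends on later fever, which biases against a drug that prevents fever; timing from admission dilutes the effect further

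*Protocol*

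**What the plan says.** Table 1 of the Protocol lists, for inpatients only and up to day 60, the secondary endpoint "Duration of pyrexia in days (defined as a temperature" of 38°C or more). Section 7.1.3 fixes its analysis in four rules.

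- **Time origin:** "time from developing pyrexia (taken as the date of admission to hospital if present at randomisation").
- **Analysed set:** "Participants who never develop pyrexia will not be included in this analysis".
- **Competing event:** deaths in the 60 days "prior to resolution of pyrexia, will be considered as having had a competing risk at the date of death".
- **Model:** "analysed using Fine and Gray regression incorporating terms for study arm and the minimisation factors used for randomisation".

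Fever is not required at entry; the relevant criterion in section 3.2 is "Exhibiting symptoms associated with COVID-19". It is not a minimisation factor in section 3.4 either; the list there ends with "WHO COVID ordinal severity score at baseline (2 or 3; 4"). Section 7.1.3 gives no fever analysis covering all randomised inpatients and no comparison of how often fever occurs.

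**The concern.** The analysed set joins two groups. Inpatients febrile at randomisation are defined before allocation, so comparing the arms among them is protected by randomisation. Inpatients who become febrile later are defined after allocation, by an event that an antiviral may change. A patient whose fever is prevented has the best possible result on this endpoint, yet leaves the analysis. If the prevented fevers are mostly short, those left in the experimental arm are longer on average, and the drug appears to slow resolution.

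The time origin is a separate matter. A patient febrile at randomisation cannot, by definition, have resolved before randomisation. Days from admission to randomisation are therefore untreated days without possible events, added to each such patient's duration. The 96-hour limit in section 3.3 runs from the COVID-19 test, so this interval has no direct upper limit.

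At stake is the direction and size of one named secondary efficacy result.

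**Working it through.** The Protocol gives no fever rates and no design figure for this endpoint. Its only design figure, 302 patients, belongs to the primary endpoint. The proportional-odds formula with the Protocol's control percentages and odds ratio 1.95 gives 290 for a fixed design. Simulating the stated interim boundaries gives 90.2% power at 302. That figure stands and does not depend on what follows.

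**1. Arithmetic illustration (all rates assumed).** Take 100 inpatients per arm, 60 febrile at randomisation with mean duration 3 days in both arms. Of the other 40, controls have 8 new fevers of 1 day and 8 of 4 days. The drug prevents the 8 short ones and changes nothing else.

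- Planned set, control: (60×3 + 8×1 + 8×4)/76 = 220/76 = 2.89 days.
- Planned set, drug: (60×3 + 8×4)/68 = 212/68 = 3.12 days.
- All inpatients: 220/100 = 2.20 versus 212/100 = 2.12 days.
- Febrile at randomisation only: 3 versus 3 days.

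The planned set makes the drug look worse (resolution hazard ratio about 0.92), although total fever days are fewer.

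**2. Simulation of the rule as written.** Assumptions, varied over ranges: 30–70% febrile at randomisation; 40% of the remaining controls develop fever; the drug multiplies that risk by 0.25 to 1; typical fever 4 days; mean lag from admission to randomisation 2 or 4 days; 5% deaths. With complete follow-up to day 60, Fine and Gray regression equals a Cox model that keeps deaths in the risk set. An sHR above 1 means faster resolution.

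| Assumed drug effect | Clock from randomisation (onset for new fevers) | Clock from admission, lag 2 | Clock from admission, lag 4 | Change in fever days, all inpatients |
|---|---|---|---|---|
| None | 1.00 | 1.00 | – | 0.00 |
| Resolution 1.5-fold faster, no prevention | 1.46 | 1.39 | 1.28 | −0.92 |
| Prevents new fevers uniformly, risk ×0.75 to ×0.25 | 1.00 | 0.98 to 0.93 | 0.96 to 0.89 | −0.20 to −0.59 |
| Prevents mainly short, mild fevers | 0.99 to 0.90 | 0.98 to 0.87 | – | −0.03 to −0.20 |

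The second row isolates the clock: it dilutes and does not reverse. The third row shows how clock and selection combine. With 50% febrile at randomisation, the analysed share is 0.50 + 0.50×0.40 = 0.70 in controls and, at risk ×0.25, 0.50 + 0.50×0.10 = 0.55 on drug. The proportion carrying days from before randomisation is then 0.50/0.70 = 71% versus 0.50/0.55 = 91%. The fourth row shows selection biasing the estimate even without the admission clock.

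**3. Prevention together with faster resolution** (30% febrile at randomisation, risk ×0.25 in milder patients, lag 2).

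| Speed of resolution | Planned sHR | Change in fever days, all inpatients |
|---|---|---|
| 1.0 | 0.87 | −0.20 |
| 1.1 | 0.93 | −0.44 |
| 1.2 | 0.99 | −0.64 |
| 1.3 | 1.04 | −0.81 |

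Restricting to patients febrile at randomisation, timed from randomisation, gives 1.00 at speed 1.0 and 1.14 at speed 1.2.

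**4. At trial size.** In the worst case of this grid (sHR 0.87), 73% of trials with 75 inpatients per arm give an estimate below 1, and 9% show nominally significant harm. With 151 per arm, which would need every patient to be an inpatient, the figures are 79% and 12%. A two-sided 5% test of a drug with no effect would show harm in about 2.5%.

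**The case against.** A reader might infer that the whole analysis is not a randomised comparison. The Protocol does not support that. Patients febrile at randomisation are a baseline subgroup and may be most of the analysed set: 60 of 76 and 60 of 68 in the illustration. Nor does the rule create a false effect, since a drug that does nothing gives sHR 1.00.

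A reader might also infer that the admission clock breaks randomisation. It does not. The lag is fixed before allocation and balanced in expectation, so alone it only attenuates.

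The reversal needs particular conditions: the drug must prevent fever and do little for fevers already present. In the illustration it must stop every short new fever and no long one, for a gain of 2.20 − 2.12 = 0.08 fever days per inpatient. A hazard ratio of 0.92 with 76 and 68 events has a standard error of about √(1/76 + 1/68) = 0.17 on the log scale, so Z = −0.083/0.17, about −0.5. That is well within chance in one trial. With prevention and 1.3-fold faster resolution the direction is right again (1.04).

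All of this stands and limits the point. It does not remove it. At 1.2-fold faster resolution with prevention, the planned estimate is 0.99 while fever days fall by 0.64, so a real benefit is hidden. The exclusion and the time origin are written into the Protocol, so an analysis plan that follows them inherits both.

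**Conclusion.** The point holds in limited form. For inpatients afebrile at randomisation, inclusion depends on an event after randomisation. If favipiravir prevents fevers, the estimate is biased against it, and a benefit can be hidden or, with little effect on existing fevers, reversed. Timing from admission separately dilutes a true effect, and adds to the selection bias when new fevers are prevented.

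The mechanism follows directly from section 7.1.3. The size does not: sHR of roughly 0.87 to 0.98 for prevention alone under the admission clock, and 1.46 reduced to 1.39 or 1.28 for the clock alone, rest on assumed fever rates and lags. A claim that the planned analysis will make an effective drug look harmful would go too far. This is one secondary endpoint in inpatients; the primary analysis, the interim boundaries and the 302 patients are unaffected. It should be corrected, because the correction is cheap.

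**What to change.** In section 7.1.3:

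- Restrict the Fine and Gray analysis to inpatients with temperature of at least 38°C at randomisation.
- Start the clock at randomisation in both arms.
- Keep death before resolution as the competing event.
- State how time after discharge is handled. The inpatient schedule has daily observations only on days 1–10. Discharged patients move to the outpatient schedule, which has telephone contact on days 1–10 and observations only at screening and days 15, 29 and 60.
- Report new fever after randomisation by arm, among all inpatients afebrile at randomisation.

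A comparison of fever days from randomisation in all inpatients, with zero for those never febrile, is suitable only as a supportive analysis. It needs a rule for deaths, since an early death would otherwise score few fever days and look like a success. It also needs a rule for missing temperatures after discharge, which treatment may influence.

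The cost is a change of wording, with no new assessments. The downside is a smaller analysed set.

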### **7.1.4 Exploratory Endpoint Analysis**

#### Duration of hospitalization (inpatients only)

This will be summarised using a Cumulative Incidence Function plot and analysed using Fine and Gray regression incorporating terms for study arm and the minimisation factors used for randomisation. (Gray, 1988, a class of k-sample tests for comparing the cumulative incidence of a competing risk. Annals of Statistics 1988; 16:1141-1154)(Fine, 1999, A proportional hazards model for the subdistribution of a competing risk. Journal of the American Statistical Association 1999; 94:

496-509). Patients who die during the course of the 60 day study period (if still in hospital) will be considered as having had a competing risk at the date of death.

#### Change in viral load

Viral load will be summarised and compared between treatment groups using an area under curve (AUC) approach standardised for the period on study and using the baseline value as a covariate.

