#### 4.3.3 Viral Load for pharmacodynamics

A nasopharyngeal swab will be collected and sent to local Academic laboratories for processing. Viral PCR testing will be conducted according to local procedures.

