## **9.5 PK/PD data analysis**

Pharmacokinetic and Pharmacodynamic analyses will be performed by The Pharmacy department, University of Strathclyde, and the University of Glasgow Translational Pharmacology Laboratory respectively.

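### The viral-load AUC comparison leaves out the minimisation factors that every other between-arm regression carries, which costs precision on an exploratory endpoint

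*Protocol*

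**What the plan says.** Section 7.1.4 (Change in viral load) compares the arms by an AUC approach, "standardised for the period on study and using the baseline value as a covariate". No other model term is named.

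Section 3.4 states the allocation method: "A minimisation algorithm incorporating a random component will be used to allocate patients to either experimental or control arm". The factors are site, age group, hypertension or obesity, symptom duration, sex, and baseline WHO severity score grouped as 2 or 3 against 4. In Appendix 1, scores 2 and 3 are ambulatory and 4 is in hospital without oxygen.

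The other between-arm regressions all carry these factors: the primary model (7.1.2); the logistic models, the pyrexia model and the WHO-score models at other days (7.1.3); and outpatient viral clearance and length of stay (7.1.4). The length-of-stay model, for example, is specified as "incorporating terms for study arm and the minimisation factors used for randomisation".

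On measurement, section 4.3.3 says "A nasopharyngeal swab will be collected and sent to local Academic laboratories for processing" and then "Viral PCR testing will be conducted according to local procedures". Section 9.5 assigns the pharmacokinetic and pharmacodynamic analyses to the pharmacy department, "University of Strathclyde, and the University of Glasgow Translational Pharmacology Laboratory respectively", which is one laboratory for pharmacodynamics.

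**The concern.** When allocation is balanced on factors that predict the outcome, the treatment estimate varies less than a model without those factors assumes. The reported standard error is then too large and the test rejects too rarely.

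Viral load has specific reasons to depend on two of the factors.

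- **Setting, closely tracked by baseline WHO score.** The inpatient table schedules viral-load swabs on days 1, 3, 8, 10, 15, 29 and 60 (section 4.2.1 also lists day 13). The outpatient table has screening and days 8, 15, 29 and 60, with day 8 optional and possibly self-taken at home. The inpatient baseline is taken close to the first dose. The outpatient baseline is the screening swab, in a window that opens four days before day 1.
- **Site.** If assays are local, site may carry differences in calibration or detection limit.

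At stake is power on the only quantitative between-arm comparison of viral load in an antiviral trial. No false claim of benefit is at stake.

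**Working it through.** **The plan's own figure.** The only sample-size figure, 302 patients, belongs to the primary ordinal endpoint. The Whitehead formula per arm is 6(1.960 + 1.282)² / [(ln 1.95)² (1 − Σp̄³)]. With the percentages in section 7.1, 1 − Σp̄³ ≈ 0.978, so it gives 6 × 10.51 / (0.446 × 0.978) ≈ 144.6, or 289 in total for a fixed design. Applying the stated interim boundaries to 302 patients gives 90.1% power by simulation. The figure reproduces and does not depend on this point. No figure is stated for viral load.

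**Assumed inputs, none from the documents.**
- 302 patients, half of them inpatients, with allocation balanced within laboratory and setting.
- SD of 1.0 log10 for AUC and 1.5 for baseline, with correlation ρ of 0.3 or 0.6.
- A setting shift d in AUC, and d/2 in baseline.
- A laboratory shift that is the same at baseline and follow-up, with 1, 3 or 6 laboratories.
- True effect 0.4 log10.

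**With the terms fitted.** The residual variance is 1 − ρ² and SE = 2√(1 − ρ²)/√302. For ρ = 0.3 this is 2 × 0.954/17.38 = 0.110. For ρ = 0.6 it is 2 × 0.8/17.38 = 0.092.

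**Baseline only, one laboratory.** The setting shift adds d²/4 to the AUC variance, d²/16 to the baseline variance and d²/8 to their covariance. The residual variance becomes (1 + d²/4) − (1.5ρ + d²/8)²/(2.25 + d²/16).
- d = 0.3, ρ = 0.3: 1.0225 − 0.46125²/2.2556 = 0.928. Divided by 0.91 this is 1.020, so the SE is 1.0% too large.
- d = 0.8, ρ = 0.6: 1.16 − 0.98²/2.29 = 0.741. Divided by 0.64 this is 1.157, so the SE is about 7.6% too large. The simulation gave 7.5%.

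**Simulated results (1,500 trials per scenario).** Extra patients = (1 + SE excess)² − 1.

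| Laboratory SD / setting shift (log10) | SE excess, 3 or 6 laboratories | Equivalent extra patients | SE excess, one laboratory (setting shift only) |
|---|---|---|---|
| 0.3 / 0.3 | 2.6–3.3% | 5–7% | 1.0–1.1% |
| 0.5 / 0.5 | 6.7–8.7% | 14–18% | 2.7–3.1% |
| 0.8 / 0.8 | 15–18% | 33–39% | 6.7–7.5% |

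With no shifts the excess is zero. Bias was below 0.01 log10 in every scenario. With six laboratories and ρ = 0.3, power without and with the terms was 94.2% and 95.8% at 0.5/0.5, and 90.5% and 96.1% at 0.8/0.8.

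**Under the null (six laboratories, ρ = 0.6).** The baseline-only test rejected in 3.5% of trials at 0.5/0.5 and 3.0% at 0.8/0.8, against a nominal 5%. With the terms the rates were 4.8% and 5.2%. The run with no shifts gave 6.0% for both models, so these rates carry simulation noise of about a percentage point. As a check at 0.5/0.5, an SE 7.8% too large moves the effective cut-off to 1.96 × 1.078 = 2.11, a two-sided rate of about 3.5%.

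The calculation covers laboratory and setting only. Any gain from age, sex, symptom duration, or hypertension or obesity is not included.

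**The case against.** The strongest reply is that section 7.1.4 gives a short outline of an exploratory analysis, does not say that baseline is the only covariate, and can be completed in a statistical analysis plan that is not shown here. The endpoint has no power claim and no role in stopping. The error is conservative, so it cannot favour the drug. All of that is right about weight. It does not remove the point: the protocol chose to name covariates for this model, and the set it names differs from all the neighbouring models without a reason.

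A reader might infer more than the documents support.

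- **That several laboratories are established.** Section 4.3.3 uses the plural, but 9.5 names one pharmacodynamic laboratory, 4.2.2 refers to a single research laboratory, and 4.3.4 leaves processing details to a Laboratory Manual that is not shown. Section 3 calls the study single-centre, although site is a minimisation factor and other sections describe several sites. The number of laboratories is open, so the need to move to a central assay is not shown.
- **That the trial randomises by laboratory and by inpatient status.** It minimises on site and WHO score, which are proxies.
- **That laboratory differences stay wholly in the error.** An offset present at both baseline and follow-up is partly absorbed by the baseline covariate.
- **That added terms cure the schedule difference.** Standardising for time on study already deals with part of it. Inpatients discharged early move to the outpatient schedule, and no baseline term puts AUCs from different swab days on a common grid.

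**Conclusion.** The point holds as a minor one about consistency and precision. As written, the viral-load comparison omits site, baseline WHO score and the other minimisation factors that every other between-arm regression in 7.1.2 to 7.1.4 includes. It would report too large a standard error whenever those factors predict viral load. The treatment estimate is unbiased and the test conservative.

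The size rests wholly on assumed variances: a standard error about 3% to 18% too large with several laboratories, 1.0% to 7.5% with one, and nothing if viral load does not differ by site or setting. The missing model terms stand whichever way the laboratory question is settled. That question is a matter for clarification and not an established defect.

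**What to change.** 1. In section 7.1.4, specify the viral-load AUC model with study arm, baseline viral load and the minimisation factors, in line with the other models. This costs nothing in data collection, since the factors are recorded at randomisation. Very small sites may need a pooling rule.
2. Reconcile sections 4.3.3 and 9.5 by stating where viral load is assayed and whether one quantitative method is used. This is a text change.
3. If more than one laboratory or assay is used, add a laboratory term where site does not already capture it. This requires only that the laboratory be recorded with each result.
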